### Sample size and randomization

We assumed that the cumulative incidence of regression to normoglycemia at two years would be 18% in the control group (based on unpublished data from the K-DPP trial) and that there would be a 50% relative risk in conversion to normoglycemia with the intervention. The sample size required in each study group was 475 with a type 1 error of 5%, at least 80% power, a contamination rate of 15%, and a 10% loss to follow-up. The sample size required with same estimates and 90% power in each group is 625, and will be recruited, if logistically feasible.

The estimated sample size of 950 participants will be randomly allocated in a 1:1 ratio to the control group and the intervention group using a computer-generated randomization sequence using Microsoft excel by an independent statistician not involved in the trial. The independent statistician will generate the randomized sequence and allocate the individuals to the randomized groups. The participants and the Principal Investigator (EM) will be blinded to the allocation sequence until informed written consent for study participation is obtained. The outcome assessors, data entry personnel and statisticians who analyse the data will be blinded throughout the study as they are not part of the team that delivers intervention or manage the project.

This study uses individual randomization in order to avoid the methodological challenges of cluster randomization, including the clustering effect on statistical power and selection bias, possibility of imbalanced study groups, and the dilution effect
^
23
^. Trial conduct solutions will be put in place to address potential contamination, if any, between the study groups with individual randomization. This include using different staff for each group, education of the participants against contamination
^
23
^, and getting signed nondisclosure agreement from the intervention participants regarding the type of intervention being received. Furthermore, analytical methods that adjust for contamination will also be used. We will also quantify the contamination using a treatment fidelity framework based on the criteria advocated by the Behaviour Change Consortium
^
24
^ and NICE guidance on behaviour change
^
25
^.

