### Intervention delivery

The intervention will be delivered through 12 sessions (individual and group based), one session per month, over a period of 1 year (
Table 3). Intervention delivery will be supported using pretested and piloted educational materials such as flip charts for group-based sessions and a mobile based application for individual sessions. The mobile application will also serve as an interactive platform for a personalized diet planning and reporting.

The group sessions (45–60 minutes duration) will be organised in the participants’ neighbourhood, mostly in homes or local health centres, delivered by the research team (postgraduates in public health/ social work degree) in the initial phase, followed by trained volunteers as “peer mentors”. Peer mentor, a group nominated volunteer, will undergo a five-day capacity building training program to guide and assist the participants in making realistic goals for lifestyle modification with the support of the extended community stakeholders.

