### Data analysis

Data will be collected and entered using a data entry template in an ODK platform by the data collectors and managed in a cloud-based server which will only be accessed by the Principal Investigator (EM). Subsequent to the data collection, the data will be used only using a participant identity number and all the personal identifiers will be masked. Only deidentified data will be shared with other investigators, if required. Data quality will be ensured during data collection and data analysis. During the data collection, the research team will verify the data for missing values and if present, will be rectified then and there. Furthermore, randomly identified 5% of the participants data will be verified with the participants through telephone for quality check. The data from the ODK platform will be exported to SPSS and data cleaning will be done manually. Any outliers or implausible values will be identified and will be checked with participants over phone, if necessary.

The analysis will follow the intention-to-treat (ITT) principle. Characteristics of the participants at baseline will be compared between study groups using descriptive statistics. The primary outcome will be analysed using the generalized estimating equations (GEE) with an appropriate working correlation structure and a binomial family with 'log' link function to estimate the relative risk (and 95% confidence interval [CI], p value). Standard errors will be based on Huber-White sandwich estimator, which will provide valid CIs even in case of misspecification of the correlation structure
^
50
^. For secondary outcomes, continuous variables will be analysed using mixed-effects linear regression models, which will include all available data at baseline, 12 and 24 months. Study group (intervention vs. control), timepoint (follow-up vs. baseline) and a study group-by-time point interaction will be specified as fixed effects. Random effects will be specified for wards, to account for the clustered study design, and for participants, to account for correlation between the repeated measurements on the same individual. Categorical variables will be analyzed using log-binomial models. All p values reported will be 2 tailed, and a p of 0.05 will be considered statistically significant. Analyses will be performed with
Stata version 14.2 (StataCorp LP, College Station, Texas, USA). 

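### Group delivery in one arm creates clustering that individual randomization does not avoid; the sample size makes no allowance for it and the secondary models do not represent it

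*Protocol article*

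**What the plan says.** Under Sample size and randomization, the protocol article gives its reason for randomizing individuals: "This study uses individual randomization in order to avoid the methodological challenges of cluster randomization, including the clustering effect on statistical power". The same section assumes that "the cumulative incidence of regression to normoglycemia at two years would be 18% in the control group" and that "there would be a 50% relative risk in conversion to normoglycemia with the intervention". From these it derives 475 women per group for 80% power at the 5% level, after allowing for 15% contamination and 10% attrition. For 90% power the figure is 625 per group. No ICC, group size or design effect is listed.

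Under Intervention delivery: "The intervention will be delivered through 12 sessions (individual and group based), one session per month". Group sessions are held in the participants' neighbourhood, and each group nominates a volunteer as peer mentor. The session schedule (Table 3) has five group sessions, with the remaining seven led by the peer mentor. Table 2 adds walking or other activity groups. Under Study groups, controls receive a leaflet and no contact beyond the 12- and 24-month assessments.

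Under Data analysis, the primary outcome is analysed by "generalized estimating equations (GEE) with an appropriate working correlation structure", a log link and Huber-White standard errors. The article says these give valid intervals even if the correlation structure is misspecified. The clustering unit is not named. For continuous secondary outcomes, "Random effects will be specified for wards, to account for the clustered study design", with a second random effect for participants; the model includes an arm-by-time interaction. Categorical secondary outcomes use log-binomial models with no clustering term stated.

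**The concern.** Randomizing individuals removes the between-ward variance that would enter the arm comparison if wards were randomized. It does not remove correlation created after randomization, when women in one arm share sessions, a mentor and activity groups. This is an individually randomized group-treatment design with clustering in the intervention arm only.

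Two things are at stake. First, the variance of the intervention-arm proportion is larger than the sample size calculation assumes. Second, a model that does not represent this correlation gives standard errors that are too small. A random intercept shared by both arms and constant over time cannot represent an effect that arises in one arm after baseline.

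**Working it through.** **Reproducing the plan's N.** Inputs from the article: 18% in controls; a 50% relative increase, so 27% (read literally as a relative risk of 0.5, the figures do not reproduce); two-sided 5%; 15% contamination; 10% loss. The two-proportion formula with continuity correction gives 359 per arm at 80% power and 473 at 90%.

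- 359 / (0.85 × 0.90) ≈ 470, against 475 stated.
- 473 / (0.85 × 0.90) ≈ 619, against 625 stated.

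Both agree to within about 1% with a design effect of 1.

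**Design effect.** DE = 1 + (m − 1) × ICC, in the intervention arm only. Neither m nor the ICC is in the article. Assumption: m from 10 to 19 and ICC from 0.01 to 0.05. The upper m follows from 950 / 25 wards / 2 arms = 19, with one group per ward.

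**Power.** The plan's allowances leave 475 × 0.85 × 0.90 = 363 per arm. Without continuity correction, power = Φ(0.09/SE − 1.96), where SE = √[(0.18 × 0.82 + DE × 0.27 × 0.73)/363]. With DE = 1, SE = √(0.3447/363) = 0.0308, and power is 83%.

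**Required N.** The stated N is scaled by the ratio of [1.96 √(0.225 × 0.775 × (1 + DE)) + z √(0.1476 + 0.1971 × DE)]² to its value at DE = 1. Here z is 0.84 for 80% power and 1.28 for 90%.

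**Type I error if the group correlation is ignored.** Under no effect the average variance inflation is (1 + DE)/2, so the error is 2[1 − Φ(1.96/√((1 + DE)/2))].

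| m | ICC | DE | Power at 475 | N for 80% | N for 90% | Type I error |
|---|---|---|---|---|---|---|
| 10 | 0.01 | 1.09 | 81% | 498 | 655 | 5.5% |
| 10 | 0.02 | 1.18 | 79% | 520 | 685 | 6.0% |
| 10 | 0.05 | 1.45 | 74% | 587 | 774 | 7.7% |
| 19 | 0.01 | 1.18 | 79% | 520 | 685 | 6.0% |
| 19 | 0.02 | 1.36 | 76% | 565 | 744 | 7.1% |
| 19 | 0.05 | 1.90 | 66% | 698 | 923 | 10.4% |

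**Primary GEE, by clustering unit.** Simulation of the log relative risk with 25 wards, 17 evaluable women per arm per ward, one delivery group per ward and 18% in both arms gave:

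- Participant clusters: type I error 5.6%, 6.7% and 9.6% at ICC 0.01, 0.02 and 0.05.
- Ward clusters, normal reference: about 6.3–6.8% at every ICC, and 6.5% at ICC 0. This excess comes from having few clusters. For comparison, P(|t| > 1.96) on 24 df is 6.2%.
- Ward clusters with a W/(W − 1) correction (W = number of wards) and t on 24 df: 4.6–5.1%.

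**Secondary mixed model.** Consider the arm difference in change from baseline to 24 months, with 25 × 17 = 425 women per arm and complete data. Illustrative variances are 0.5 for participant, 0.5 for residual and 0.05 for a delivery-group effect present only at follow-up. Ward and participant intercepts cancel from the change, so the model's variance is 4 × 0.5/425 = 0.00471, an SE of 0.069. The true variance adds 0.05/25 = 0.0020, an SE of 0.082. A time-constant ward-by-arm intercept also cancels, and a generalized least squares check gave 0.069 with or without it. A group effect that applies at follow-up gave 0.082.

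**The case against.** A reader might infer that the primary confidence interval is certainly too narrow because of the group effect. The article does not support that. It specifies a sandwich estimator, and elsewhere names wards as its source of clustering. If the GEE clusters on ward and delivery groups lie within wards, the sandwich covers the group correlation, leaving only the few-cluster excess. The clustering unit may also be settled in an analysis plan that is not shown, so its absence is not itself a fault. What stands is that the article's general assurance of valid intervals holds only for correlation inside the declared cluster and with enough clusters.

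A reader might also see a flat contradiction between the randomization rationale and the later reference to a clustered design. Part of that dissolves: the rationale compares individual with cluster randomization, and the later phrase fits the sampling of wards. The rationale is still wrong in implying that the effect of clustering on power has been avoided.

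Nor is power shown to be below 80% whatever the ICC. At 0.01 the stated power essentially holds. The ICC is uncertain: only five of the twelve sessions are group sessions, and the outcome is measured 12 months after the programme ends. Against this, the other seven sessions are led by the group's own mentor, so they too can induce correlation. How contamination should enter the calculation is a separate question, and the figures here keep the plan's own allowance.

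**Conclusion.** The point holds in a conditional form. Clustering arises in the intervention arm, the sample size allows nothing for it, and the stated reason for individual randomization overlooks it. The secondary mixed and log-binomial models, as described, would understate standard errors if outcomes are correlated within delivery groups. For the primary analysis, error is inflated materially only with participant clusters and an ICC of about 0.02 or more. With uncorrected ward clusters it is slightly above nominal for a different reason. All magnitudes rest on assumed group sizes of 10 to 19 and ICCs of 0.01 to 0.05. They are small at the low end: power falls from 83% to 79–81%. At the high end it falls to 66–74%.

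**What to change.** 1. Declare the ward as the cluster for the primary GEE and the secondary log-binomial models, with a small-sample correction and a t reference on about 24 df. State that delivery groups are nested within wards, and qualify the sentence on sandwich validity.
2. In the mixed models, add an intervention-arm delivery-group random effect that applies at follow-up (group by time), or use ward-clustered, small-sample-corrected standard errors. A time-constant ward-by-arm intercept would change nothing. The ward-clustered option also needs no term that exists in one arm only, which could reveal allocation to the blinded analyst.
3. Delete the claim that the clustering effect on power is avoided. Restate power with an intervention-arm design effect over a stated group size and ICC range.

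The trial is still in screening, so the cost is analysis wording and a restated power figure. The downside is slightly wider intervals and a less favourable stated power. The article already plans to recruit 625 per arm if feasible. That number exceeds the 80% power requirement in the table except for groups of 19 at ICC 0.05.

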### Recruitment of participants and data collection

Screening and recruitment of participants and data collection will be conducted in 2 stages as described below:

**
*Stage 1: Home visits*.** All women in the age group of 30–60 years will be selected from the voters' list of the selected wards. Eligibility for participation in the study will be ascertained during home visits using a screening questionnaire (includes demographics and eligibility criteria) by trained staff. Only one participant per household (randomly selected) will be screened. Those who meet the eligibility criteria and provide consent for study participation will be screened with a point-of-care glucometer (OneTouch Select Plus, LifeScan Inc.) and their waist circumference will be measured using SECA 201 ergonomic retractable tape with using a standard protocol
^
26
^. Those who are overweight or obese (waist circumference ≥80 cm)
^
22
^ and with a random capillary blood glucose of >110 mg/dl
^
27
^ will be invited to undergo a 2-hr OGTT in clinics organized in their neighbourhoods. These individuals will be considered to be at high risk for having prediabetes or diabetes.

**
*Stage 2: Clinics*.** The high-risk individuals will attend clinics organized in their neighbourhoods, where they will undergo a 2-hr OGTT, body composition, anthropometric, and blood pressure measurements, and interviews to complete the questionnaires. Those diagnosed with T2DM on the OGTT will be referred to the nearby health facility for treatment and care. Body fat composition will be assessed using TANITA DC 360 (pole). Blood pressure will be measured using an OMRON HEM-7120 blood pressure monitor using the standard protocol
^
26
^.

The weight and height will be measured using SECA 813 flat scale and SECA 213 stadiometer, respectively, with a standard protocol
^
26
^. Blood samples will be collected in a fasting state (8–10 hours of fasting) and will be centrifuged within 30 mins after collection and transported to a lab accredited by the National Accreditation Board for Testing and Calibration Laboratories (NABL)
^
28
^. Questionnaires will be administered by trained staff to collect information on demographics, diet
^
29
^, physical activity
^
26
^, tobacco use
^
26
^, alcohol use
^
26
^, diabetes knowledge
^
30
^, prediabetes knowledge
^
31
^, health-related quality of life (HRQoL)
^
32
^; self-efficacy for managing chronic diseases
^
33
^, risk perception for diabetes
^
34
^, social support
^
35
^, and sleep hygiene
^
36
^ using standardized questionnaires (
Table 1). Those who are diagnosed with diabetes at 12
^th^ and 24
^th^ month assessment will be referred to the nearby health facility for treatment and care, and will continue to participate in the trial. All assessments done at the baseline will be repeated at 12 months and 24 months.

**Table 1. T1:** Outcomes, measurement tools, and data collection time points.

Outcome measures	Variable	Tools/tests used	Baseline	Regular assessment	12 months	24 months
Primary outcome for effectiveness						
Regression of i-IFG to normoglycemia at 12 and 24 months	Fasting plasma glucose and 2-hr post-load plasma glucose	OGTT in a NABL accredited laboratory ^ 28 ^	✓		✓	✓
Secondary outcomes for effectiveness						
Incidence of diabetes	Fasting plasma glucose, 30 minutes and 2-hr post- load plasma glucose, HbA1c	NABL accredited laboratory ^ 28 ^	✓		✓	✓
Insulin sensitivity	Fasting insulin, 2-h insulin, Homa IR	NABL accredited laboratory ^ 28 ^	✓		✓	✓
Beta cell function	Fasting insulin, 2hr insulin, Homa B		✓		✓	✓
Lipid profile	Total cholesterol, triglycerides, HDL-cholesterol, and LDL-cholesterol	NABL accredited laboratory ^ 28 ^	✓		✓	✓
Liver function tests	Aspartate aminotransferase (AST), alanine aminotransferase (ALT), gamma-glutamyl transferase (GGT)	NABL accredited laboratory ^ 28 ^	✓		✓	✓
Blood Pressure	Systolic and diastolic blood pressure	OMRON electronic blood pressure monitor	✓		✓	✓
Anthropometrics	a. Weight b. Height c. Waist circumference	a. SECA weighing scale b. SECA stadiometer c. SECA non-elastic tape	✓		✓	✓
Body composition measures	a. Fat percent b. Muscle mass	TANITA body fat analyser	✓		✓	✓
Psychosocial variables	a. Diabetes knowledge b. Knowledge on prediabetes c. Health-related quality of life d. Self-efficacy/self-empowerment e. Risk-perception for diabetes f. Social support g. Sleep Hygiene	a. 24 Item Diabetes Knowledge Questionnaire ^ 30 ^ b. Prediabetes Knowledge Questionnaire ^ 31 ^ c. WHO QoL BREF scale ^ 32 ^ d. Health Lifestyle and Personal Control Questionnaire ^ 33 ^ e. Scale by Hivert *et al.* ^ 34 ^ f. Scale by Sarason *et al.* ^ 35 ^ g. Sleep Hygiene Index scale by Mastin *et al.* ^ 36 ^	✓		✓	✓
Behavioural outcomes for effectiveness and implementation						
	a. Diet b. Physical activity and sedentary behaviour c. Tobacco use d. Alcohol use	a. Food frequency questionnaire ^ 25 ^ b. Global Physical Activity Questionnaire ^ 26 ^ c. WHO STEPS questionnaire ^ 26 ^ d. WHO STEPS questionnaire ^ 26 ^	✓		✓	✓
Implementation outcomes (at community, provider and beneficiary levels)						
	a. Reach a1. Participants approached a2. Frequency of contact with the *panchayat* b. Effectiveness b1. Improved knowledge on T2DM prevention b2. Risk perception b3. Self-efficacy b4. Social Support c. Adoption c1 Individuals attending the sessions (Number) c2. Individuals who set goals c3 Individuals achieving the behavioural targets c4. Change in knowledge on diabetes and its risk factors and behavioural targets d. Implementation d1. Peer mentor trainings (quality) d2. Participants group sessions (quality) d3. Sessions conducted d4. Peer mentor selection d5. Support received by peer mentors e. Maintenance e 1. Individuals achieving behavioural targets	a1. Database on recruitment a2. Database on meetings b1. 24 Item Diabetes Knowledge Questionnaire ^ 30 ^ b.2. Risk perception Scale ^ 34 ^ b.3 Health Lifestyle and Personal Control Questionnaire ^ 33 ^ b4. Social Support scale ^ 35 ^ c1. Participant attendance data c2. Participants feedback report c3. Behavioural change report ^ 24, 25 ^ c4. Pre and post knowledge change evaluation report (Participant) d1. Peer mentors feedback report, Pre and post knowledge change evaluation report (Peer Mentors) d2. Participants feedback report, d3. Session attendance data d4. 1. Peer mentors characteristics d5. Participant feedback report e1. Behavioural assessment data ^ 24, 25 ^	✓ ✓ ✓ ✓	✓ ✓ ✓ ✓ ✓ ✓ ✓ ✓ ✓ ✓ ✓	✓ ✓ ✓ ✓	✓ ✓ ✓ ✓ ✓

OGTT- Oral Glucose Tolerance Test, NABL-National Accreditation Board for Testing and Calibration Laboratories, WHO QoL BREF- World Health Organization Quality of Life , HDL- High density lipoprotein, LDL- Low density lipoprotein

Staff conducting physical measurements and administering questionnaires at baseline and follow-up visits will be blinded to participants’ group allocation. Intervention staff will not be engaged in the data collection process and the statistician engaged in data analysis will be blinded to the group allocation.

All study materials can be found in the
*Extended data*
^
37
^.

### Outcomes

The primary outcome for the effectiveness study will be normoglycemia, defined as FPG<5.6 mmol/l and 2-hr PG<7.6 mmol/l, at 24 months
^
3
^. Secondary outcomes will include incidence of T2DM (fasting plasma glucose ≥ 7.0 mmol/l or 2hr PG ≥ 11.1 mmol/l or HbA1c ≥6.5%), insulin sensitivity, beta cell function, weight, body mass index, waist circumference, FPG, 2-hr PG, blood pressure, body composition measures (fat percent and muscle mass) and psychosocial variables (health-related quality of life, self-efficacy/self-empowerment, risk-perception for diabetes, social support and sleep hygiene). Implementation outcomes include reach, effectiveness, adoption, implementation and maintenance of the intervention
^
16
^.

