## Abstract

**Background:** Isolated impaired fasting glucose (i-IFG) constitutes a major group in the prediabetic spectrum among Indians, and thus it is imperative to identify effective diabetes prevention strategies. This study aims to evaluate the effects of an intensive community-based lifestyle modification program on regression to normoglycemia among women with i-IFG, compared to a control group at 24 months. The study also aims to evaluate the implementation of the intervention, via both process and implementation outcomes.

**Methods:** We will use a hybrid design (Effectiveness-implementation hybrid type 2 trial) to test the effectiveness and implementation of the lifestyle modification intervention. Effectiveness is evaluated using a randomized controlled trial among 950 overweight or obese women, aged 30 to 60 years, with i-IFG on an oral glucose tolerance test in the Indian state of Kerala. The intervention involves an intensive lifestyle modification program through group and individually mentored sessions using behavioural determinants and behavioural change techniques.  The intervention group will receive the intervention for a period of 12 months and the control group will receive general health advice through a health education booklet. Data on behavioural, clinical, and biochemical measures will be collected using standard methods at 12 and 24 months. The primary outcome will be regression to normoglycemia at 24 months, as defined by the American Diabetes Association criteria.

**Discussion**: This study will provide the first evidence on the effects of lifestyle interventions on regression to normoglycemia in people with i-IFG among Indians.

**CTRI registration:** CTRI/2021/07/035289 (30/07/2021)

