### Study participants

**
*Inclusion criteria*:** 1) Women aged 30–60 years; 2) overweight or obese (waist circumference ≥80 cm)
^
22
^; 3) no prior history of diabetes; 4) not taking any glucose-lowering medications; 5) no prior history of gestational diabetes mellitus (GDM); 6) able to read, write and speak Malayalam, the local language; 7) consents to participate in the trial; and 8) diagnosed with i-IFG (fasting plasma glucose [FPG] 5.6-6.9 mmol/l and 2-hr plasma glucose [2-hr PG] <7.8 mmol/l) on a 2-hr oral glucose tolerance test (OGTT)
^
3
^.

**
*Exclusion criteria*:** 1) Women with known T2DM; 2) having GDM; 3) prior history of GDM; 4) breastfeeding women; 5) having major chronic illnesses including mental disorders, that are likely to impede consenting and participation in the intervention program; 6) taking medications that could alter glucose metabolism (e.g., corticosteroids); and 7) diagnosed with normoglycemia, IGT, and T2DM, as per the American Diabetes Association criteria
^
3
^ on the OGTT.

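### The primary endpoint requires a 2-hour glucose below 7.6 mmol/l, but the entry criterion under the same reference accepts values below 7.8 mmol/l as normal

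*Protocol article*

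**What the plan says.** Four places in the protocol article bear on the 2-hour limit.

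- **Outcomes:** the primary effectiveness outcome is "normoglycemia, defined as FPG<5.6 mmol/l and 2-hr PG<7.6 mmol/l, at 24 months", with reference 3 cited.
- **Study participants, inclusion criterion 8:** isolated impaired fasting glucose is "fasting plasma glucose [FPG] 5.6-6.9 mmol/l and 2-hr plasma glucose [2-hr PG] <7.8 mmol/l" on an oral glucose tolerance test, with reference 3 cited again.
- **Study participants, exclusion criterion 7:** women are excluded if "diagnosed with normoglycemia, IGT, and T2DM, as per the American Diabetes Association criteria", again under reference 3.
- **Abstract:** "The primary outcome will be regression to normoglycemia at 24 months, as defined by the American Diabetes Association criteria".

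Table 1 lists the fasting and 2-hour variables for the primary outcome but gives no cut-off. No section explains why the endpoint limit differs from the entry limit.

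The section on sample size assumes that 18% of controls regress by two years, from unpublished data of the Kerala Diabetes Prevention Program. It adds that "there would be a 50% relative risk in conversion to normoglycemia with the intervention". It does not say which 2-hour limit the 18% rests on.

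**The concern.** One reference is credited with two upper limits for a normal 2-hour value, and the lower one sits in the primary endpoint. Two groups of women are affected.

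1. A woman with fasting glucose below 5.6 mmol/l and a 2-hour value from 7.6 to just under 7.8 mmol/l at 24 months no longer has impaired fasting glucose. Her 2-hour value is one the trial accepts as unimpaired at entry. She is nevertheless scored as not regressed, and no category is left for her.
2. A woman may enter with a 2-hour value in that same band, bring down the fasting glucose that qualified her, keep her 2-hour value unchanged, and still fail. The endpoint then asks her to lower a value that was called normal at baseline.

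The analysis is also exposed. A programmer who follows the Outcomes section uses 7.6. One who follows the Abstract and the entry criteria uses 7.8. The same data then give two primary results, and a choice made after the data are seen would be a post hoc decision on the endpoint.

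**Working it through.** **Step 1: the two limits side by side**

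| 24-month result (mmol/l) | By the entry limits | By the Outcomes section |
|---|---|---|
| Fasting <5.6, 2-hour <7.6 | both values normal | regressed |
| Fasting <5.6, 2-hour 7.6 to <7.8 | both values normal | **not regressed** |
| Fasting <5.6, 2-hour ≥7.8 | 2-hour value not normal | not regressed |
| Fasting ≥5.6, any 2-hour value | fasting value not normal | not regressed |

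The two definitions differ in one row only. The ADA figure for normoglycemia is not printed in the protocol, and the comparison does not need it, because the entry criterion applies 7.8 under that reference.

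**Step 2: how many women might fall in the band**

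The protocol gives no distribution of 2-hour glucose. The figures here are an assumption: among women with fasting glucose below 5.6 mmol/l, 2-hour glucose is normal with mean m and standard deviation s. The share lost among women below 7.8 is

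f = [Φ((7.8 − m)/s) − Φ((7.6 − m)/s)] / Φ((7.8 − m)/s)

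| m | s | Φ at 7.6 | Φ at 7.8 | f |
|---|---|---|---|---|
| 6.0 | 1.1 | 0.927 | 0.949 | 2.3% |
| 6.5 | 1.1 | 0.841 | 0.881 | 4.5% |
| 6.8 | 1.0 | 0.788 | 0.841 | 6.3% |

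**Step 3: reproduce the planned sample size**

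Inputs from the section on sample size: 18% in controls, and per group "475 with a type 1 error of 5%, at least 80% power, a contamination rate of 15%, and a 10% loss to follow-up". The stated effect is read as a relative risk of 1.5, so the intervention rate is 0.18 × 1.5 = 27%. Tests are two-sided (Data analysis).

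n = [1.96 √(2 p̄(1 − p̄)) + 0.842 √(p1(1 − p1) + p2(1 − p2))]² / (p2 − p1)²

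With p1 = 0.18, p2 = 0.27 and p̄ = 0.225, n = 337. The continuity correction, (n/4)[1 + √(1 + 4/(n(p2 − p1)))]², raises this to 359. Inflating for contamination and loss gives 359 / (0.85 × 0.90) = 470 per group, against 475 stated. At 90% power the same steps give 473 and then 619, against 625 stated. Both agree to about 1%, so the reading of the inputs is sound. Taking the effect as a relative risk of 0.5 gives 296, or 323 with the correction, and does not match.

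**Step 4: effect on the design**

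Assume that 18% and 27% are the rates under the 7.8 limit and that a share f is lost equally in both arms. Both rates are multiplied by (1 − f) and the relative risk stays at 1.5.

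| f | Control rate | Intervention rate | n per group, 80% power |
|---|---|---|---|
| 0 | 18.0% | 27.0% | 470 |
| 1% | 17.8% | 26.7% | 476 |
| 2% | 17.6% | 26.5% | 482 |
| 5% | 17.1% | 25.7% | 501 |
| 10% | 16.2% | 24.3% | 536 |

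For the range in step 2 (2.3% to 6.3%) the requirement is about 484 to 510. In women, 475 × (0.18 + 0.27) = 214 expected regressors before loss to follow-up, and 214 × 0.023 to 214 × 0.063 is about 5 to 13 reclassified as failures.

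**The case against.** The other side can say that 7.6 is most likely a one-digit slip for 7.8 rather than a chosen threshold. The band is only 0.2 mmol/l wide, the same limit applies to both arms, and outcome assessors are blinded. If both arms lose the same share, the relative risk does not move and the required sample size rises little. The band share rests on a distribution found nowhere in the protocol. The planned rates fall only if the 18% was derived under the 7.8 limit, which the protocol does not say. The 27% is itself a reading of loosely worded text.

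Most of this stands. The size is illustrative, the fall in event rates is conditional, and a typing error is the likeliest explanation. The text of the registration is not in the documents, so it can only be checked. None of this removes the contradiction. Both limits are in the current text, both cite the same source, and nothing in the protocol says which governs. A likely slip in a primary endpoint threshold still has to be corrected, since it would otherwise be carried into the analysis as written.

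**Conclusion.** The concern holds. The primary endpoint as stated contradicts the trial's own entry limit and its description as ADA-defined. It misclassifies women with a normal fasting value and a 2-hour value from 7.6 to just under 7.8 mmol/l.

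The numerical effect is probably small: about 2% to 6% of women who would otherwise count as regressed, under the assumed distributions, and no shift in the relative risk if the loss is equal across arms. An unequal loss would move the relative risk, and the documents do not allow that to be sized.

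The importance comes from where the error sits. The threshold of the only primary effectiveness endpoint must have one reading before outcome data are seen.

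**What to change.** - In the Outcomes section, define the primary outcome as fasting glucose below 5.6 mmol/l and 2-hour glucose below 7.8 mmol/l at 24 months, which is the protocol's own limit for a normal 2-hour value.
- Use the same limit in the analysis code, and check the trial registration against it.
- If 7.6 was intended, give the reason, stop describing the endpoint as ADA-defined, and state how women with 2-hour values from 7.6 to just under 7.8 mmol/l are classified at baseline and at follow-up.
- Confirm which 2-hour limit underlies the 18% control rate, so that the design assumption and the endpoint match.

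The cost is one figure in the protocol and a check of the registration and code. The protocol reports that the trial is still screening, so no new data are needed.
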